### Medication review

The individualised medication review involved the intervention nurse drawing up a chart of the participant's prescribed medications as documented by the research assistant at the enrolment visit (T1), which included the generic and brand name of the medication, what the medication was for, the dose and when to take it, and targets for which to aim. Targets included a blood pressure ≤130 mmHg, blood glucose of < 7 mmol/L, Hb A_1C _< 7%, and low density lipoprotein (LDL) cholesterol < 2.5 mmol/L as recommended by Harris [18]. Prescription reconciliation, the process of comparing the participant's reported medication regimen to all of the medications that the participant has been taking, was conducted. Any areas of ambiguity with what participants thought they should be taking compared with what was prescribed according to pill containers and medication lists were sorted prior to obtaining agreement of the prescription. For example, one participant was taking duplicate cholesterol-lowering drugs that were the same but had different brand names. The medication chart was left with the participants as their personal medication record to take to medical consultations if they did not have a current medication list, and to note changes in their prescriptions as they occurred.

### DVD development

The DVD involved an interactive, psychosocial approach to motivating people to take their medications, appealing to knowledge, thoughts and feelings, underpinned by the modified Health Belief Model [15]. By focusing on the attitudes and beliefs of individuals, we believed a person would be more likely to take their medications as prescribed if they understood the inter-relationship of their conditions, in particular hypertension, and if their confidence in independently managing their health was improved.

The content of the DVD was drawn from analysis of medication adherence from the perspectives of consumers with co-existing diabetes and chronic kidney disease and health professionals likely to care for this group [19]. Knowledge of these aspects is likely to facilitate effective communication between consumers and health professionals, and contribute to medication safety and improved wellbeing [20]. The DVD comprised three sections: how blood pressure affects the body; the need, benefit and safety of prescribed medications; and tips to help consumers take their medications as prescribed. Video clips of participants with co-existing diabetes and chronic kidney disease not involved in the RCT who were willing to share their experiences with taking multiple medications were incorporated into each section. These participants talked about how they managed their medication regimens on a daily basis to facilitate medication adherence using a psychosocial approach. As a result it was hypothesized that participants in the trial would control their blood pressure and learn effective medication self-management skills.

The content of the DVD was checked against information in the public arena to ensure a consistent message was being conveyed. We also made sure that the text could easily be read by consumers with visual impairment (≥ 24 Arial font) and understood at a Year 8 level. The DVD was developed under guidance of the project team and a reference group drawn from the key stakeholders of participants and health professionals engaged in the research.

The DVD underwent formative evaluation for internal validity by nine health professionals, one educational expert, and one consumer who provided video footage. Content, readability (flow, clarity, language, layout), and appropriateness of information to meet the learning objectives and desired outcomes were critically evaluated using the Content Validity indices [21], which were respectively 0.98, 0.95 and 0.97. These values exceeded the parameter of 0.83 for item acceptability. Overall, comments were very positive, and included constructive editorial suggestions. Advice was also obtained on screen design features and navigation of the interface, which were incorporated into the final version. The DVD was produced by the university's biomedical multimedia unit incorporating educational design expertise.

### Motivational interviewing telephone calls

Fortnightly telephone calls were planned after the intervention home visit until follow-up at 3-months post-baseline (T2). Each call was conducted using the principles of motivational interviewing by the intervention nurse to promote medication adherence, adapted from the guidelines of Dilorio et al. [22]. The telephone call commenced with an open-ended question inquiring about the participants' wellbeing. An enquiry about their blood pressure followed, whereby participants reported their blood pressure readings for discussion. A general enquiry was then made about their medications, such as whether any changes were made to their medications, if they experienced any side effects or difficulties taking their medications, if they have any concerns with doctors' visits and if they had any questions regarding their health.

The participants' motivation and confidence in taking their medications was then assessed out of a score of 1 to 10, using this information to elicit barriers, concerns and positive self-motivational statements. A summary of these comments was presented back to the participant, inviting any further comments using reflective and normalising statements where appropriate to elicit problem-solving. The participants was then asked to identify three goals they would like to achieve in the next five years to help link their medication adherence to their life. They were also asked to briefly explore connections between their current medication-taking behaviour and their ability to achieve these goals. A summary was presented back to the participants, incorporating suggestions to overcome identified difficulties and affirming desired behaviour. The participants were asked if they had any queries which were addressed, and the call was concluded after thanking the participants for their time and interest. The remaining motivational interviewing calls followed a similar format that incorporated follow-up of suggestions or queries made in previous calls.

### Usual care

Participants randomized to the usual care control group received standard care offered to patients with co-existing diabetes and chronic kidney disease attending the diabetes and nephrology outpatients' clinics at the hospital and primary care offered by their general practitioners. Our definition of standard care is the ongoing medical care provided to a patient with co-existing diabetes and chronic kidney disease attending routine outpatient clinic follow up, which has been reported elsewhere [23]. Data were collected from the usual care group at the same time points as the intervention group.

### Feasibility of study

In the planning stages of the study in 2006, we found that more than 1,400 patients with diabetes at the hospital where recruitment was to take place had urine microalbumin/creatinine ratios ranging from 2 to an extreme of 6020 mg/mmol, with an average microalbumin/creatinine ratio of 97 mg/mmol suitable for our recruitment purposes. Additionally, the renal department at the hospital is one of the largest renal services in Australia treating in excess of 2,300 patients annually with chronic kidney disease. The base rate of systolic blood pressure control > 130 mmHg in the nephrology outpatient clinic population was estimated to be about 50%.

### Setting and recruitment

A research assistant who was a qualified registered nurse recruited from the diabetes and nephrology outpatient clinics of a metropolitan hospital in Melbourne commencing in August 2008. This research assistant conducted all data collection for the study and was a different person to the intervention nurse. There were two diabetes clinics per week for patients requiring ongoing review with approximately 50 patients booked in per clinic. If the patient did not have hypertension, they were immediately deemed ineligible irrespective of the presence of renal disease. There was one renal clinic per week with approximately 50 patients booked in of whom about 15 had either type 1 or type 2 diabetes. Participants were also recruited from a combined diabetes and nephrology clinic (NephDiab clinic) established to incorporate both diabetes and nephrology specialist review within the same appointment where approximately 20 patients were booked in every month. Patients who met the inclusion criteria were approached by the research assistant and asked if they wanted to participate in a study designed to help them understand and manage their complex medical conditions and prescribed medications better.

### Patient eligibility

The inclusion criteria for the MESMI study are listed in Table 1. The primary outcome was systolic blood pressure control, taken by the research assistant who was trained to take blood pressure according to accepted guidelines [17] using an Accosson mercury desk sphygmomanometer and 3M™ Littmann classic 11 S.E. stethoscope. Participants were to avoid smoking, exercise and caffeine for 30 minutes while they were waiting for their clinic consultation and were seated for approximately five minutes prior to having their blood pressure measured.

**Table 1 T1:** Inclusion and exclusion criteria for the MESMI study

Inclusion criteria	
*****	Patients of either gender aged ≥ 18 years of age
*****	Able to comprehend English (English proficiency test > Not at all)
*****	Mentally competent (Abbreviated Mental Test score > 6)
*****	Type 1 or Type 2 diabetes recorded in patient's medical record
*****	Chronic kidney disease defined by an estimated Modified Diet in
*****	Renal Disease glomerular filtration rate (MDRD-eGFR) of ≤ 60 mL/min/1.73 m^2 ^and/or:
*****	Diabetic kidney disease defined by Malb/Cr ratios > 2.0 mg/mmol for men, > 3.5 mg/mmol for women or an elevated 24 hour urine albumin of > 30 mg over 24 hours
*****	Systolic hypertension ≥130 mmHg for the previous two clinic visits & prescribed antihypertensive medication/s
	

**Exclusion criteria**	

*	Impending dialysis defined by an eGFR less than 15 mL/min/1.73 m^2^
*	Pregnancy
*	A new diagnosis of cancer
*	A mental illness not stabilized with medication

The participant's blood pressure was taken by the research assistant five times at recruitment, commencing with once on either arm in the sitting position. The blood pressure measurement was then repeated twice on the arm with the lower systolic blood pressure at one minute intervals. These two blood pressure readings were then averaged, and the mean measure was used to check the presence of hypertension. Finally, the standing blood pressure was then taken on the same arm within three minutes to detect the presence of orthostatic hypotension, a common side effect of antihypertensive medications in the older population [17].

Consumers who were not mentally competent (assessed by a score of < 6 on the Abbreviated Mental Test) [24], had an unstable mental illness, or did not understand the English language sufficiently were excluded. Proficiency in spoken English was assessed by asking participants from non-English speaking backgrounds how well they spoke English using a four-point scale ranging from very well to not at all [25]. Persons who spoke English not well who had a support person with a good command of the English language were included whereas persons who scored 'not at all' on the Proficiency in Spoken English Test, irrespective of the presence of support persons who spoke English, were excluded from the trial.

### Ethics approval and data and safety monitoring

Prior to commencing the study, ethics approval was sought and granted from the Human Research Ethics Committees of the participating hospital (HREC Project No: 2006.239) and university (Ethics ID: 0713622). The trial was prospectively registered with the Australian and New Zealand Clinical Trials Register (ANZCTR) before recruitment of the first participant (Registration number ACTRN12607000044426). Written informed consent was obtained from participants prior to enrolment. The study was conducted according to the protocol and under ethical guidelines of the National Health and Medical Research Council of Australia [26]. Regular weekly meetings were held between members of the research team to discuss issues relating to the progress of the trial.

### Enrolment and randomization

Participants who expressed an interest in participating and who met the inclusion criteria were contacted by the research assistant by telephone to organize a home visit. At the home visit, formal informed consent was obtained prior to collecting demographic, social and medical data, sitting blood pressure according to accepted guidelines [17] (taken twice on the arm with the lowest reading a minute apart and averaged), body mass index, comorbidity burden, baseline surveys and pill counts (Table 2). The baseline visits lasted approximately 1 1/4 hours each.

**Table 2 T2:** Schedule of data collected from consumers at each data collection point

Measures	T1	T2	T3	T4
Demographics(age, gender, education, usual role, social support)	X			
English proficiency	X			
Abbreviated mental health test	X			
Chronic conditions	X			
Prescribed medications	X			
Body Mass Index	X			X
Blood pressure	X	X	X	X
SF-12v2-Item Health Survey	X	X	X	X
MASES Self-Efficacy Scale	X	X	X	X
Morisky scale	X	X	X	X
Health care utilisation scale	X	X	X	X
Pill count	X	X	X	X
Serum & urine laboratory measures ie eGFR, urine Malb/Cr ratios, creatinine, Hb, HbA_1C_, CaPO4, lipids	X	X	X	X

All participants have data collected at four points in time (Table 2): baseline (T1), 3-month following the baseline data collection and at completion of the intervention (T2), and 6- (T3) and 9-months (T4) post-intervention (12-months post-baseline data collection). Routine clinical laboratory surrogate measures indicative of medication adherence taken as part of the participant's standard treatment such as eGFR, urine microalbumin/creatinine ratios, serum creatinine, Hb, Hb A_1C_, CaP04 and low-density lipids are collected at these four time points from the participant's medical records. Follow-up is projected to continue until July 2010.

### Instruments

The Morisky Medication Adherence Scale [27] was used to measure adherence to all prescribed medications, has four questions with 'yes' and 'no' responses and a Cronbach's α coefficient of 0.62. The Medication Adherence Self-efficacy Scale (MASES) [28] has 26 questions identifying difficult situations affecting medication self-efficacy, with 'not at all sure', 'somewhat sure' and 'very sure' answers, takes about five minutes to complete and has a Cronbach's α coefficient of 0.95. The Short Form (SF)-12, 12 item Health Survey (version 2) [29], was used to measure general wellbeing, has five choices of responses and takes approximately two minutes to complete. Cronbach's α coefficients for the SF-12 closely mirror that of the SF-36 at 0.89 and 0.76. The Health Care Utilization (HCU) [30] Scale has four items of health care, for example, visits to a doctor, where participants have to indicate the number of times they used the service in the past three months, and takes approximately two minutes to complete. The HCU has a test-retest reliability of.0.91 [9].

### Pill counts

Pill counts were conducted at T1, T2, T3 and T4 time points according to the process outlined by Haynes et al. [31]. At enrolment, participants were asked to keep their empty pill containers for the duration of the study. On each data collection home visit, participants were invited to present all their prescribed medications which were manually counted. The prescribed regimen off the container, the dispensing pharmacy, the number of tablets dispensed and the dispensing date for all tablets was recorded. The participants were asked if they kept their medications anywhere else (for example, a duplicate supply), and these were also counted and recorded. The participants were asked if they started taking pills from the containers on hand on the dispensing date, or if not, when they did start taking the medication from the container.

Pill counts were estimated by dividing the number of pills missing from the containers by the number of pills which should be missing if the participant had taken all medications as prescribed [31]. This figure was then multiplied by 100 to obtain a percentage score. For example, Adherence A = (# of pills taken/#of total doses) × 100. When more than 100% was calculated, Adherence B was calculated, which was: Adherence B = 100 - (Adherence A -100): if Adherence A was 120%, Adherence B was 80% [32].

Medication adherence was set at ≥80% as the minimum acceptable level for each prescribed medication, a commonly accepted cut-off point for defining a therapeutic level of medication adherence [33]. Insulin with different devices was hard to quantify when we did not have the resources to buy equipment to weigh the insulin. We decided to use serum blood glucose, HbA_1C _and evidence of hypoglycaemic and hyperglycaemic episodes requiring hospitalization as evidence of medication nonadherence.

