### Study design

The study is a single-site, single-blind, longitudinal RCT. Participants have been allocated to one of two groups: the intervention group receives a multifactorial intervention designed to improve blood pressure control and medication adherence, and the control group receives standard care offered by the treating hospital's outpatient clinics and primary care provided by the participants' general practitioner. Data are collected at four time points: enrolment baseline data collection (T1), immediately following delivery of the intervention (T2), three months post-intervention (T3) and 9-months post-intervention (T4).

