### Data analysis

The analysis will be performed on an intent-to-treat basis. All data will be entered into an ACCESS database by a second research assistant who is blinded to the intervention group. An experienced biostatistician will check the integrity of the database and conduct statistical analyses. Descriptive statistics will be used to summarise demographic, social and medical data between the intervention and usual care groups and any effect of these variables on primary and secondary outcomes. Baseline characteristics of the intervention and usual care groups will be compared. Blood pressure, medication adherence, medication self-efficacy, and general wellbeing between the usual care and intervention groups will be compared to assess the effects of the intervention between groups and within participants at T2, 3 and 4 using t-tests as appropriate. The various measures of medication adherence will be examined for correlations. Continuous variables that are not normally distributed will be examined using equivalent non-parametric tests. Differences in change in binary categorical variables within each group will be analysed using McNemar's test and the changes between the two groups will be assessed by chi-squared tests for trends. Potential confounders may include comorbidities and number of prescribed medications. Statistical significance will be determined with p values of < 0.05.

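### Pill-count change from T1 sets a baseline without retained empty containers against later counts that can include them, so within-arm change can shift with no change in behaviour

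*Protocol article*

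**What the plan says.** All points are in the protocol article, under Methods.

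- **When containers are kept.** Pill counts: "At enrolment, participants were asked to keep their empty pill containers for the duration of the study".
- **When pills are counted.** Same section: "Pill counts were conducted at T1, T2, T3 and T4 time points". One counting step serves every visit: "On each data collection home visit, participants were invited to present all their prescribed medications which were manually counted".
- **T1 is the enrolment visit.** Study design labels T1 as "enrolment baseline data collection (T1"), and Medication review refers to medicines "as documented by the research assistant at the enrolment visit (T1"). Enrolment and randomization places consent at a home visit, followed by baseline data that include "body mass index, comorbidity burden, baseline surveys and pill counts (Table 2").
- **How adherence is scored.** Pill counts divides pills gone from the containers by pills that should be gone. Values above 100% are reflected back below 100%, and the cut-off is 80% for each medicine.
- **How it is analysed.** Data analysis plans between-group and within-participant comparisons of medication adherence at the three follow-up visits by t-test. It adds, for binary outcomes in general: "Differences in change in binary categorical variables within each group will be analysed using McNemar's test".
- **Hypothesis 2** (Study hypotheses) is worded as greater adherence than standard care at T3.

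**The concern.** A finished pack enters a pill count only if its container still exists. Before T1 nobody had been asked to keep containers, so the T1 count rests on whatever was in the home. After T1 finished packs can be counted, and the period covered can be the whole interval since the previous visit. The planned within-participant comparison then subtracts one kind of measurement from another.

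Three features can move the result while behaviour stays constant:

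1. A short T1 window makes the percentage more variable, which changes the share above a fixed cut-off.
2. An error in a pack's start date weighs more over a short window, and reflecting values above 100% turns overshoot into apparent non-adherence.
3. A gap between packs before T1 leaves no trace if the finished pack was discarded, whereas the same gap after T1 is visible.

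The first can act either way. The second tends to produce an apparent rise after T1, and the third an apparent fall. At stake is a before-after adherence claim within an arm, tested as if it reflected behaviour.

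**Working it through.** **Step 1: timing.** The article gives no figure for pill-count change, so there is none to reproduce. The order of events is documented: T1 is the enrolment home visit, the baseline count is made there, and the request to keep empties is made at enrolment. Whether count or request came first within the visit is not stated, but it matters little. Recruitment began on 27 August 2008 and baseline visits on 8 September 2008, so even a request made at the clinic would normally have yielded only a short run of empties.

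**Step 2: scoring by hand.** Adherence A = 100 × pills gone / pills expected; if A > 100, B = 200 − A. The article's example reproduces: A = 120 gives B = 80. Take a person who misses nothing, with a start date wrong by 3 days (an assumption):

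| Window | Start recorded 3 days late | Start recorded 3 days early |
|---|---|---|
| 10 days | 10/7 = 142.9%, B = 57.1% | 10/13 = 76.9% |
| 90 days | 90/87 = 103.4%, B = 96.6% | 90/93 = 96.8% |

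Over 10 days the same error fails the 80% cut-off in either direction. Over 90 days it passes in both.

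**Step 3: simulation with constant behaviour.** Assumptions, none from the article except the 3-month T1–T2 interval (taken as 90 days): one once-daily medicine in packs of 30; daily probability p of taking it; T1 counts only the current pack, in use at least 3 days; T2 counts every pill gone over 90 days. The refill gap averages 0 or 4 days. Start-date error has SD 0 or 3 days and is applied only to on-hand counts. There were 3,000 simulated people per row, less those with no current pack in use for 3 days.

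| p | Mean gap | Date SD | Mean T1 → T2 (%) | At or above 80%, T1 → T2 (%) | Shift in share (points) |
|---|---|---|---|---|---|
| 0.75 | 0 | 0 | 74.6 → 74.9 | 33.0 → 15.3 | −17.7 |
| 0.85 | 0 | 0 | 84.4 → 85.0 | 73.2 → 92.6 | +19.4 |
| 0.95 | 0 | 0 | 94.9 → 95.0 | 98.0 → 100 | +2.0 |
| 0.85 | 4 | 0 | 84.1 → 76.6 | 71.7 → 24.9 | −46.8 |
| 0.85 | 0 | 3 | 75.2 → 85.1 | 52.1 → 92.3 | +40.2 |
| 0.85 | 4 | 3 | 75.7 → 76.5 | 51.2 → 23.8 | −27.4 |

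The refill-gap mean can be checked in closed form. A pack lasts 30/p days, so long-run adherence is 30/(30/p + 4). For p = 0.85 this is 30/39.29 = 76.4%, against 76.6% simulated.

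If T2 is also an on-hand count, the p = 0.85 case with no gap and exact dates gives means of 84.4% and 84.4%, and shares of 73.2% and 72.1%. Across all settings on-hand shares at the two visits differed by up to 5.6 points (67.0% against 61.4%), so shifts of that size in the table mean nothing.

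**Step 4: what McNemar's test could do, if applied to the 80% outcome.** A second simulation let adherence vary between people (mean 90%, Beta with concentration 20), with a T1 window of 3–30 days, a T2 window of 90 days, and date error at both visits. There were no refill gaps, so it can show only the upward case. With date error SD of 1, 2 or 3 days, the share at or above 80% went from about 78%, 67% or 57% to about 90%. In one arm of 54 (108/2), repeated runs gave p < 0.05 in about 35–41%, 84–86% or 97–98% of trials with no real change. With exact dates the shift was 3–6 points. If T1 stock already spanned 30–90 days, it was at most about 2.5 points.

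**Step 5: between arms.** Randomisation follows the baseline visit, so the T1 method is the same in both arms, and later counts follow one process. Any shift is common to both arms and cancels in expectation if empties are kept equally. A change score still carries the T1 noise: Var(T3 − T1) = σ₁² + σ₃² − 2ρσ₁σ₃, which is below σ₃² only if ρ > σ₁/(2σ₃). If σ₁ is twice σ₃ or more, no correlation achieves that. With T1 as covariate, the data set its weight.

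**The case against.** The strongest reply is that the article never says kept empties enter the later counts. It describes one process, one formula and the dating of containers at hand, and refers to a cited method for the rest; such detail is often left to a full protocol. If later counts also used on-hand containers only, the shift largely disappears. That stands as a limit. But retaining containers has no other evident use, and no later instruction can give T1 the retained containers it lacked.

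Several further objections also stand:

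- The discussion of assessing adherence reports six part-used boxes of one medicine in some homes and several storage places, so a single short T1 pack does not describe everyone. Dispensing dates were recorded too, so dating does not rest on recall alone, although the article says very few participants could recall start dates.
- The 80% cut-off is set per medicine, and the McNemar sentence does not name pill counts. The false-positive rates above are therefore conditional on a participant-level use that the article does not spell out.
- The Morisky scale and laboratory markers do not depend on containers.

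A reader might infer that change from T1 must move, or must move upwards. The documents do not support this: direction and size depend on quantities they do not give, and the mean can stay put. A reader might also infer that hypothesis 2 is biased. It is worded as a T3 comparison between randomised arms, and nothing in the article shows the arms keeping empties differently.

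**Conclusion.** The point holds in a limited form. T1 pill counts were made without retained empties and later counts can include them, so within-participant and within-arm change from T1 cannot be read as change in adherence. The artefact can be upward, downward or absent. The simulated range of about −47 to +40 points in the share at or above 80% shows what is possible under stated assumptions and does not estimate what happened in this trial. The conclusion assumes that kept empties are counted from T2 onwards, which is inferred. Hypothesis 2, tested as a between-arm comparison at T3, is unbiased by this if retention is equal in the two arms. The matter concerns a secondary outcome and should be corrected in the analysis wording.

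**What to change.** In Data analysis:

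- Test hypothesis 2 by comparing arms on T3 pill-count adherence with T1 adherence as a covariate, not as a change score.
- Do not test pill-count change from T1 within arms, whether by paired test or McNemar's test. If it is shown, label it descriptive and say that T1 was collected without retained empties.
- Restrict any within-arm time trend in pill-count adherence to T2 to T4.
- State in Pill counts whether kept empties enter the T2 to T4 counts.

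This needs no new data or visits. The cost is the loss of a tested before-after adherence figure for each arm.
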